### Study size

For sub-grouping analyses using machine learning methods, the approach of Foreman [87, 88] to calculate the sample size is used: 2^k^ (where k = number of variables) is minimum sample size and 5*2^k^ is the most conservative sample size. The UK Biobank data study [31, 89] provided only a sub-set of the required parameters, thus the impact of the additional measures in our proposed study (e.g. spine MRI) on sub-grouping is unclear. In this preliminary work [31], less than seven variables were required to characterise a LBP collective, with two specific variables being most important for defining sub-groups. Thus, we argue that using up to 8 variables (2^8^ = 256) across spinal tissue, nervous system and psychosocial domains will likely be sufficient to detect the largest and clinically relevant sub-groups. Therefore, we conservatively target a sample of 300 people with non-specific LBP and 100 controls. This will enable valid subgrouping/classification of patients with non-specific LBP with up to 8 variables in the primary analysis, with additional power for sub-domain analyses with less variables as required. The choice of a 3:1 ratio LBP-to-control was pragmatic for project feasibility and because the focus of our project is on sub-grouping in LBP rather than in pain-free controls.

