**Fig 1 pone.0282346.g001:**
[figure not shown]
Approach to artificial intelligence tool implementation. GOÄ: Gebührenordnung für Ärzte (German medical cost database).

Dimensionality reduction will be performed to identify the most relevant variables (of those listed; Table 1) for subgrouping and classification. Given known challenges with data-analytic variable weighting and multidimensional data (e.g. scaling each variable to 0–1) [31], our first step in dimensionality reduction will focus on traditional statistical methods including paired t-tests, analysis of covariance and multicollinearity assessment through correlation analysis [31]. Following this, pending the number of important variables (e.g. if more than 8 variables remain) we will consider variable weighting using a decision tree classifier and targeted projection pursuit with artificial neural networks [91]. The outputs will be used to select the most relevant variables distinguishing non-specific LBP from controls (2-class model).Following determination of the most important variables, pain-free controls will be removed from the data for the following clustering steps. Cluster validation methods [92], including Calinski-Harabasz, Davies-Bouldin and Sillouette values, will be used to determine the optimal number of clusters and variables for the remaining non-specific LBP data. Given the potential for high dimensionality introducing noise and influencing clustering, we will evaluate the outputs of clustering using all outcomes and within individual domains (e.g. in preliminary work [31, 47], psychological and brain MRI variables correlated more highly with each other within their domains than between variable domains). The output of this step will allow us to determine the optimal number of clusters and variables.Based on the information in step B, we will apply fuzzy c-means clustering model [31] of non-specific LBP on either the primary clustering or domain specific clustering. The clusters derived in this step will be used to label classes of non-specific LBP.Outputs from steps B and C in terms of class labels will be used to evaluate non-specific LBP classification. We will apply Support Vector Machine, Naïve Bayes, k-Nearest Neighbour and Random Forest binary/multiclass classifiers as appropriate for the data. Given we are focusing on internal (i.e. on the current dataset, rather than a second newly collected dataset from a different research centre or project) validation of a classification model, validation of the model will be done via k-fold cross validation, as random data-splitting is not generally recommended for internal model validation [93–96]. The output of this will be a sub-grouping tool for people with non-specific LBP assuming availability of all data and tests and no consideration of test cost.We will consider the following sensitivity analyses:

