
we will evaluate random data-splitting and repeat steps B and C to determine if the clustering outputs hold across random samples;we will apply steps B to E within each domain (e.g. brain MRI, psychosocial variables, spine MRI) as required;repetition of analysis only with participants without any imputed data; to examine the potential impact of missing data.consideration of impact of secondary variables (see bottom panel of Table 1) on sub-grouping.the methods of step (D) will be reapplied under constrained cost assumptions, considering financial-cost, time, and patient burden of obtaining each clinical outcome. Financial costs will be according to current rates according to the Gebührenordnung für Ärzte; time will be according to clinical measure and patient burden will be according to an ordinal scale. The output will be a model for most effective sub-group identification for people with non-specific LBP respecting cost/time/burden constraints.consider the findings of sub-grouping when patients with or without radiological evidence of degenerative changes (see Quantitative variables and data collection > Spine MRI) are included.

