## Discussion

Based on our recent systematic review [23], our project will be the first larger scale study to assess multiple dimensions of pain contributors with a view to detecting clinically relevant sub-groups in non-specific LBP. We anticipate the production of a comprehensive, multidimensional dataset including imaging of the lumbar spine and the brain, assessment of pain processing, and emotional and psychosocial determinants of pain. This dataset will position us to test the hypothesis that patients with non-specific LBP can be grouped in clusters with common features.

Currently non-specific LBP is viewed as one large all-encompassing diagnostic entity. In our view, the results of the project, if sub-groups do indeed exist, will result in a substantial departure from the current paradigm by taking a fresh, rational perspective to optimise the screening of NSCLBP, which will guide more focused and tailored management. Importantly, should no relevant sub-groups be detected, this will also be a boon for current efforts, in that this will reinforce the need to implement current (generic) approaches, such as reducing medical imaging, for the management of non-specific LBP.

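### Steps B to D have no route to a finding of no sub-groups: the three named indices start at two clusters, and no threshold or reference stops the chain

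*Protocol article*

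**What the plan says.** Under Analytical and statistical methods, step A selects variables that separate people with low back pain (LBP) from controls, and the controls are then dropped. In step B, cluster validation methods "including Calinski-Harabasz, Davies-Bouldin and Sillouette values, will be used to determine the optimal number of clusters and variables for the remaining non-specific LBP data". The step ends: "The output of this step will allow us to determine the optimal number of clusters and variables". Step C applies fuzzy c-means, and "The clusters derived in this step will be used to label classes of non-specific LBP". Step D trains several classifiers on those labels, validates them by k-fold cross-validation and delivers the sub-grouping tool.

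One sensitivity analysis bears on the clusters themselves: "we will evaluate random data-splitting and repeat steps B and C to determine if the clustering outputs hold across random samples". No level of agreement is attached to it.

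The Discussion states the purpose as to "test the hypothesis that patients with non-specific LBP can be grouped in clusters with common features". It also provides for the opposite result: "should no relevant sub-groups be detected, this will also be a boon for current efforts", because that would support continued generic management.

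**The concern.** The Discussion presents a question with two possible answers, but the analysis steps lead to only one. The indices rank solutions with two or more clusters against each other. They do not compare the best of these with no clustering at all. Labelling and classification then follow whatever step B returns.

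If non-specific LBP is a continuum on the measured variables, the procedure as written still divides it into classes and produces a tool that assigns patients to them. The article expects the tool to be taken up in practice and to support trials in the sub-groups, so an arbitrary cut could steer that work. The two planned checks, random splitting and cross-validation, can both look favourable in that situation.

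**Working it through.** **Inputs from the protocol article.** Study size gives 300 people with LBP ("we conservatively target a sample of 300 people with non-specific LBP and 100 controls") and up to 8 variables. Its rule reproduces: 2^8 = 256, below the 300 targeted. That figure only sets the dimensions used here; the point does not dispute it.

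**The indices at one cluster (k = 1).**
- Calinski-Harabasz = [B/(k − 1)] / [W/(n − k)], where B and W are the between- and within-cluster sums of squares. At k = 1, B = 0 and k − 1 = 0, so the numerator is 0/0.
- Davies-Bouldin averages, over clusters i, the maximum over j ≠ i of (S_i + S_j)/M_ij. At k = 1 there is no j.
- Silhouette = (b − a)/max(a, b), where b is the mean distance to the nearest other cluster. At k = 1 there is no other cluster.

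This result is exact and needs no assumption about the data.

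**What the steps do when there are no sub-groups.** I simulated one multivariate normal population with n = 300 and 8 variables scaled 0 to 1. The search ran over k = 2 to 6, with 60 data sets per setting, using fuzzy c-means (FCM, fuzzifier 2) and k-means. The normal form, the search range and the common pairwise correlations are my assumptions; the article gives none of them. For the split check, two-cluster centres were fitted in each random half of 150, all 300 people were labelled from both sets, and agreement was measured by the adjusted Rand index (ARI).

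| Correlation | Method | Calinski-Harabasz picks 2 | Davies-Bouldin picks 2 | Silhouette picks 2 | Mean best silhouette | Median split ARI |
|---|---|---|---|---|---|---|
| 0 | FCM | 58/60 | 0/60 | 57/60 | 0.10 | 0.08 |
| 0 | k-means | 60/60 | 0/60 | 48/60 | 0.11 | 0.09 |
| 0.3 | FCM | 60/60 | 60/60 | 60/60 | 0.21 | 0.85 |
| 0.3 | k-means | 60/60 | 60/60 | 60/60 | 0.21 | 0.79 |
| 0.5 | FCM | 60/60 | 60/60 | 60/60 | 0.28 | 0.84 |
| 0.5 | k-means | 60/60 | 60/60 | 60/60 | 0.28 | 0.83 |

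Where an index did not pick 2, it picked 3 to 6. FCM sometimes filled fewer clusters than requested (78, 32 and 4 of 5 × 60 = 300 fits at correlations 0, 0.3 and 0.5), but every index still named a k of at least 2 in every data set.

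**Why the split repeats.** With common correlation r among p variables, the largest eigenvalue of the correlation matrix is 1 + (p − 1)r and the others are 1 − r. With p = 8 these are 1 and 1 at r = 0, 1 + 7 × 0.1 = 1.7 and 0.9 at r = 0.1, and 1 + 7 × 0.3 = 3.1 and 0.7 at r = 0.3. Once one axis dominates, both halves are cut across it. Two further sets of runs gave mean split ARIs of 0.10 and 0.07 at r = 0, 0.46 and 0.52 at r = 0.1, and 0.73 and 0.76 at r = 0.3; the first set gave 0.66 at r = 0.2.

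**Cross-validation in step D.** In one Gaussian population (n = 300, 8 variables, FCM with two clusters, 40 data sets per setting), mean 10-fold accuracy in predicting the derived labels was 94% (r = 0) and 97% (r = 0.3) for Naïve Bayes, and 88% and 93% for k-nearest neighbour. High accuracy is therefore expected when no sub-groups exist.

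**The case against.** A reader might infer that the study is certain to declare false sub-groups, a false-positive rate of 100%. The documents do not support that. The list of validation methods is introduced as open-ended. The Discussion speaks of relevant sub-groups, so clusters could be returned and then judged weak or unimportant. Index values also have size as well as rank: a best silhouette of 0.10 to 0.28 could be reported as weak structure. All this stands against the stronger claim. None of it supplies a rule, so the judgement would be made after seeing the data. Nor does a silhouette value interpret itself: with 2 variables instead of 8, the same homogeneous population gave mean best values of 0.35 to 0.41.

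A reader might also infer that the random-split check is worthless. It is not. With nearly uncorrelated variables it shows the clusters to be unstable. Step A includes a collinearity assessment, and the article's preliminary work found higher correlation within the psychological and brain imaging domains than between domains. Uniform correlation of 0.3 across the primary variable set is therefore not a given. The same remark makes the problem most plausible for the within-domain clustering, which is planned in step B and again in the sensitivity analyses.

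Finally, a statistical analysis plan may exist and could hold thresholds. A missing cut-off alone would not be a finding. The finding is that the article names the deciding indices, passes their result on without condition, and announces a result those steps cannot return.

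**Conclusion.** The point holds in this form: the written algorithm always gives at least two labelled classes and a classifier, while the article says it tests whether clusters exist. That the named indices cannot evaluate one cluster is a mathematical fact. How far the planned checks mislead depends on correlations that the article does not state. In a single homogeneous population, split-half agreement ran from about 0.1 at correlation 0, through about 0.5 at 0.1, to about 0.7 to 0.85 at 0.3 or more. Cross-validated accuracy cannot settle whether sub-groups exist at any of these values. This bears on the study's central hypothesis and should be settled before the data are analysed.

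**What to change.** Before step C, add one cluster as a candidate, for the primary clustering and for each domain-specific clustering:

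1. Generate at least 200 single-population reference data sets that keep the observed marginal distributions and correlations of the LBP data, for example a Gaussian copula with empirical marginals.
2. Run the same clustering and the same search over k on each.
3. Name one deciding index in advance, for example silhouette, and report the others as supportive.
4. Claim discrete sub-groups only if the observed best value exceeds the 95th percentile of the reference. Otherwise report no evidence of discrete sub-groups, and present any partition and classifier as descriptive only.

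A plain multivariate normal reference is not safe, because many Table 1 variables are bounded or may be skewed. On one homogeneous skewed population it gave false positives in 24/24 data sets by silhouette and 0/24 by Calinski-Harabasz, which also shows why the deciding index must be named. The copula reference gave 3/50 (6%) and 0/50. It still detected a 30% sub-group shifted by 2 SD at correlation 0 in 25/25 data sets, and one shifted by 1.5 SD at correlation 0.3 in 18/25 (72%) by silhouette.

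The cost is one paragraph and some computing time, with no new data. The downsides are limited power for small or weakly separated sub-groups, and that the study may have to report none.

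### Step B uses raw cluster-validity indices to choose the number of variables and between all outcomes and single domains, but these indices are not comparable across sets of different size and tend to favour small ones

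*Protocol article*

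**What the plan says.** All references are to the protocol article, Analytical and statistical methods, unless stated.

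- **Step A** reduces the variables to those that best separate people with LBP from controls.
- **Step B** drops the controls. The three indices "will be used to determine the optimal number of clusters and variables for the remaining non-specific LBP data". The reason given for comparing sets is noise: "Given the potential for high dimensionality introducing noise and influencing clustering", the authors write, "we will evaluate the outputs of clustering using all outcomes and within individual domains". The step closes with "The output of this step will allow us to determine the optimal number of clusters and variables".
- **Step C** then applies fuzzy c-means "on either the primary clustering or domain specific clustering", and the resulting clusters become the class labels that step D learns to predict.
- **Sensitivity analyses** include random data-splitting: "repeat steps B and C to determine if the clustering outputs hold across random samples".
- **Study size**: "we conservatively target a sample of 300 people with non-specific LBP and 100 controls". It allows for up to 8 variables across the spinal tissue, nervous system and psychosocial domains.

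The article states no adjustment for the number of variables, no reference distribution and no other criterion for choosing between variable sets.

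**The concern.** All three indices are built from distances in the space of the variables being clustered. Adding variables changes those distances whether or not clusters exist: spread that is unrelated to the partition accumulates within clusters, and the indices get worse. Setting the index of an 8-variable set beside that of a 2- or 3-variable domain therefore partly compares dimension, not cluster quality.

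Step C acts on this comparison. If the comparison leans towards small sets, the sub-group labels may come from one domain when the structure runs across several. The multi-domain information that the project is designed to combine would be set aside, and patients would be assigned to sub-groups less accurately.

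**Working it through.** **Inputs.** From the article: 300 people with LBP are clustered; up to 8 variables (Study size); the three named indices; all outcomes compared with single domains (step B). Assumed, because the article gives no figures: the distributions, separations, correlations and domain sizes below. Most runs use k-means; fuzzy c-means was checked on the data without clusters and gave the same pattern.

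**The plan's own figure.** The article reports no index values. Its only related figure is the minimum sample for 8 variables: 2^8 = 256, which reproduces and lies below 300.

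**Formulas.**
- Calinski-Harabasz (CH) = [B/(k−1)] / [W/(n−k)], with B and W the between- and within-cluster sums of squares. Higher is better.
- Davies-Bouldin (DB) = the mean over clusters of the largest (S_i + S_j)/d_ij, with S the mean distance to the cluster centre and d the distance between centres. Lower is better.
- Silhouette = the mean of (b − a)/max(a, b), with a the mean distance to the own cluster and b that to the nearest other cluster. Higher is better.

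**Step 1. No clusters, by hand.** Cut one standard normal variable at its mean. The two halves account for a share 2/π = 0.637 of its variance. With p independent variables of unit variance and the same cut, B is proportional to 0.637 and W to p − 0.637, so for k = 2 and n = 300, CH ≈ 298 × 0.637/(p − 0.637):
- p = 1: 298 × 0.637/0.363 ≈ 523
- p = 8: 298 × 0.637/7.363 ≈ 26

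The partition is equally meaningless in both cases, and CH differs about twentyfold.

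**Step 2. No clusters, simulated** (independent normal variables, k = 2, n = 300):

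| Variables | CH | DB | Silhouette |
|---|---|---|---|
| 1 | 534 | 0.60 | 0.56 |
| 2 | 163 | 1.18 | 0.33 |
| 4 | 70 | 1.92 | 0.18 |
| 8 | 34 | 2.85 | 0.10 |

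k-means optimises the cut, so its CH values lie slightly above the hand calculation. With a correlation of 0.5 between variables and the best value over k = 2 to 4, the silhouette still falls from 0.56 (1 variable) to 0.28 (8).

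**Step 3. Two true groups** (40%/60%, assumed 1.5 SD apart on every variable, k = 2). ARI is the adjusted Rand index against the true groups:

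| Variables | CH | DB | Silhouette | ARI |
|---|---|---|---|---|
| 1 | 568 | 0.59 | 0.56 | 0.27 |
| 2 | 266 | 0.93 | 0.41 | 0.50 |
| 4 | 183 | 1.19 | 0.33 | 0.73 |
| 8 | 169 | 1.27 | 0.32 | 0.93 |

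The indices and the accuracy run in opposite directions.

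**Step 4. The comparison that the article describes: all outcomes against domains** (8 variables in domains of 3, 3 and 2).
- *All three domains informative, 1 to 2 SD:* the all-outcomes set won on no index in 60 runs, although its ARI was best (0.53–0.96, against 0.20–0.68 for single domains).
- *Two domains informative, the 2-variable domain pure noise* (within-domain correlation 0.3 and 0.6 respectively; 40 runs at each of four separations, 160 in all): the all-outcomes set never won. At 1.0 SD the noise domain won 40/40 on every index (ARI 0.00, against 0.41 for all outcomes). At 1.5 SD it won 34–39 of 40 (0.00 against 0.71). At 2.0 and 2.5 SD an informative domain nearly always won, with lower ARI than all outcomes (0.68 against 0.90, and 0.83–0.84 against 0.97).
- *One 3-variable domain informative, the others noise:* at 1.5, 2 and 3 SD the informative domain had the best average value on all three indices (silhouette 0.35, 0.44 and 0.59, against 0.23 and 0.32 for the noise domains). Here the comparison pointed to the right set.

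**The case against.** The strongest reply has four parts.

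**The bias is a tendency, not a law.** A reader might infer that the indices improve whenever a variable is dropped. They do not. In one-at-a-time removal from 8 variables, dropping a noise variable improved every index in 100% of cases. Dropping an informative variable while noise remained did so in 0% (two clusters) or 32–45% (three clusters), and with all 8 informative in 55–78%. From 6 to 8 informative variables at 1.5 SD the indices are flat (silhouette 0.31 to 0.32, CH 165 to 168, DB 1.27 both times). This stands.

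**The winner need not be the worst set.** A reader might also infer that the least informative set is selected. Noise can win when separation is weak, but with clear separation the winner was informative and merely incomplete. This stands too.

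**The article writes no rule that the best raw index wins, and no search down to one variable.** It is true that no all-subset search is described, so a collapse to one variable should not be read into the plan; step 4 is the relevant comparison, not the 1-against-8 contrast. But the article does name these indices as what determines the number of variables, gives no other criterion, and lets step C act on the result.

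**There are safeguards.** Step A screens the variables first, and random splitting repeats steps B and C. Step A, however, screens for separation from controls, not for structure within LBP, and a split-sample repeat applies the same uncalibrated comparison in each half, so the halves can agree on the same wrong set. These steps temper the problem without removing it.

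**Conclusion.** The point holds in this form: raw Calinski-Harabasz, Davies-Bouldin and silhouette values are not comparable across variable sets of different size and tend to favour small sets, so they cannot by themselves determine the number of variables or decide between all outcomes and single domains. That they depend on dimension needs no assumption about sub-groups, since it appears in data without clusters.

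The consequence does depend on assumptions. If structure spans domains with separations of about 1 to 2 SD, the choice leans to a single small domain and loses accuracy. If one domain clearly carries the structure, the indices can choose correctly. The article does not say which of these applies, so no single figure for lost accuracy can be given. Using the indices to choose the number of clusters within one fixed variable set is not in question.

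**What to change.** In step B, restrict the three indices to choosing the number of clusters within a variable set that is fixed beforehand. To compare variable sets, or all outcomes with single domains:

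1. For each set, generate reference data without clusters (a single cloud) with the same variables, covariance and sample size, and run the same clustering on them.
2. Express each observed index relative to that reference, as a z-score or percentile. Alternatively, compare the bootstrap stability of assignments with the stability found in the reference data.
3. State that step C chooses between the primary and the domain-specific clustering on this scale, and apply the same procedure in the random-split repeat.

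The cost is analysis wording and computing time. Recruitment, measurements and sample size do not change.

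### Step D cross-validates classifiers against labels clustered from the same people and variables, so its accuracy is high even without sub-groups and cannot show that they exist

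*Protocol article*

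**What the plan says.** The steps are set out in order in the Protocol article, Analytical and statistical methods.

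- **Step A** picks the variables that separate LBP participants from controls. The controls are then dropped.
- **Step B** chooses the number of clusters by internal indices, "including Calinski-Harabasz, Davies-Bouldin and Sillouette values, will be used to determine the optimal number of clusters".
- **Step C** fits fuzzy c-means to the LBP data: "The clusters derived in this step will be used to label classes of non-specific LBP".
- **Step D** takes those labels as its target: "Outputs from steps B and C in terms of class labels will be used to evaluate non-specific LBP classification". Support vector machine (SVM), naive Bayes, k-nearest neighbour (kNN) and random forest classifiers are fitted, and "validation of the model will be done via k-fold cross validation, as random data-splitting is not generally recommended for internal model validation". The output is called a sub-grouping tool.

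Among the sensitivity analyses to be considered is this one: "we will evaluate random data-splitting and repeat steps B and C to determine if the clustering outputs hold across random samples". Another reapplies step D under limits on cost, time and patient burden. The Discussion says the data will test whether patients fall into clusters with common features, and treats a finding of no relevant sub-groups as informative.

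**The concern.** Cross-validation guards against optimism when the outcome of a held-out person is known independently of the model. Here it is not. As the steps are ordered, each held-out person's label already exists before folds are formed, was computed with that person in the data, and is a function of the same variables given to the classifier. Good agreement is then close to guaranteed, whether the clusters are real groups or an arbitrary cut through one continuous population.

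At stake is the hypothesis in the Discussion. Following the stated steps exactly gives a validated performance figure that is high by construction, and no stated step shows what that figure would be if there were no sub-groups. The Introduction already describes earlier work as deriving sub-groups and then classifying them accurately, so it is realistic that a high step-D accuracy would be taken as support for the sub-groups.

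**Working it through.** **Inputs from the Protocol article.** Study size: "we conservatively target a sample of 300 people with non-specific LBP and 100 controls", and "using up to 8 variables (2^8^ = 256) across spinal tissue, nervous system and psychosocial domains". The plan's own figure reproduces: 2^8 = 256, below the target of 300 (the conservative version of the rule would be 5 × 256 = 1,280). The four classifiers are those of step D. The protocol states no cross-validated accuracy, so there is none to reproduce.

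**Inputs assumed, because the protocol does not give them.** 10 folds; 2 to 4 clusters; 4, 6 or 8 variables; pairwise correlation 0 or 0.3; fuzzifier m = 1.5 or 2.

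**Why the label is predictable.** In fuzzy c-means the membership of person i in cluster j is u_ij = 1 / Σ_l (d_ij / d_il)^(2/(m−1)), where d is the distance to the cluster centre. The largest membership belongs to the nearest centre. Given the centres, the label is therefore a fixed function of the person's own variables. With two clusters the boundary is a flat plane, which a classifier learns easily from about 270 people (300 × 9/10).

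**Simulation with no sub-groups.** One multivariate normal population, n = 300, standardised; labels from fuzzy c-means on all 300; then 10-fold accuracy, the share of the 300 whose held-out prediction equals the label. There were 8 repeats per setting, and a run was dropped if any cluster held fewer than 10 people. The figures are ranges of mean accuracy over settings.

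| Clusters | SVM | Naive Bayes | kNN | Random forest | Share in largest cluster |
|---|---|---|---|---|---|
| 2 | 94-97% | 94-98% | 87-93% | 89-94% | 51-53% |
| 3 | 88-95% | 88-94% | 81-91% | 83-89% | 35-47% |
| 4 | 84-93% | 82-92% | 76-88% | 75-88% | 27-48% |

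Accuracy is far above the share in the largest cluster throughout. Simulation error is about one percentage point in most settings. Cells with 8 uncorrelated variables and 3 or 4 clusters are less certain, because between 0 and 7 of 8 runs were usable.

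**Does whole-data variable selection add to this?** Choosing 8 of 45 pure-noise variables by t-test (300 against 100) gave 94.2% for the SVM with two clusters, against 94.4-94.8% for 8 uncorrelated variables without selection. It adds almost nothing; the high accuracy comes from the labels.

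**Comparison with real sub-groups.** Three well-separated clusters in 8 variables gave 97-99%.

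**Stability as an alternative.** Two random halves were clustered separately and their assignments compared by adjusted Rand index:

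- no sub-groups, uncorrelated variables: about 0.0 to 0.24
- no sub-groups, correlation 0.3: 0.37 to 0.81
- three real clusters: 0.96

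Stability discriminates better than accuracy, but correlated variables alone can make it look moderate to high.

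**Does step B fill the gap?** All three named indices compare clusters with one another and need at least two, so they cannot return one cluster as the answer. No threshold for concluding that there are no sub-groups is stated.

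**The case against.** The strongest reply is that the protocol never offers step D as proof of sub-groups. It calls it internal validation of a classification model, puts the cluster question to step B and the random-split repeat, allows for a null result, and asks for further cohort or interventional studies. A reader might infer that the protocol itself equates step-D accuracy with proof; the text does not say so, and that part of the reply stands. It does not remove the problem, because the split repeat is only to be considered, names no no-cluster reference, and does not touch step D.

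Other stronger readings also go too far:

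- **Accuracy will be about 90-97% whenever sub-groups are absent.** This fits mainly SVM and naive Bayes with two clusters. The protocol fixes neither the number of clusters nor the fold count nor the fuzzifier. With five clusters and 6 to 8 correlated variables, accuracy was 74-79%.
- **Whole-data variable selection is a second source of the inflation.** The simulation does not support this.
- **Accuracy carries no information.** With three clusters the ranges were 81-95% without sub-groups and 97-99% with well-separated ones, and these do not overlap. Accuracy carries little information, and it can be read only beside a reference.
- **Cross-validating the cost-constrained model is meaningless.** When tests are removed, the predictors no longer define the label in full. In a single-population check with naive Bayes and 2 or 3 clusters, accuracy fell from 89-98% with all 8 variables to 69-86% with 4 and 59-78% with 2. How well cheaper tests recover the assignment is a legitimate question.

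That clustering stays outside the folds is inferred from the order of the steps; it is the natural reading, not an explicit statement. Figure 1 could not be consulted.

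**Conclusion.** The point holds in limited form. Step-D accuracy mainly measures how well a classifier relearns a boundary drawn on the same people and variables. With no sub-groups it is about 87-98% for two clusters and about 75-95% for three or four, given 300 people, 4 to 8 variables, 10 folds, correlation 0 to 0.3 and fuzzifier 1.5 to 2. These ranges rest on normally distributed data and on settings the protocol does not give. They illustrate the problem and do not forecast this study's result. The random-split repeat is a partial safeguard. What is missing is a firm analysis that sets stability and accuracy against what one undivided population would produce.

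**What to change.** 1. Move the random-split check from the analyses to be considered into the main analysis. In each resample or training fold, repeat variable selection, choice of the number of clusters and clustering, then assign the held-out people.
2. Report agreement of assignments, for example adjusted Rand index and per-cluster Jaccard.
3. Set these figures, and step-D accuracy, beside the same quantities from single-population reference data with the observed correlation structure. The reference is needed because stability alone can mislead when variables correlate.
4. State that step-D accuracy, including for the cost-constrained model, describes only how faithfully a tool reproduces the cluster assignment and is not evidence that sub-groups exist.

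The cost is wording and computing time; no new data are needed. The downside is that the reported figure will probably be less favourable.
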